## Abstract

**Background:**

Preventing recurrence of depression forms an important challenge for current treatments. Cognitive control impairments often remain present during remission of depression, putting remitted depressed patients at heightened risk for new depressive episodes by disrupting emotion regulation processes. Importantly, research indicates that cognitive control training targeting working memory functioning shows potential in reducing maladaptive emotion regulation and depressive symptomatology in clinically depressed patients and at-risk student samples. The current study aims to test the effectiveness of cognitive control training as a preventive intervention in a remitted depressed sample, exploring effects of cognitive control training on rumination and depressive symptomatology, along with indicators of adaptive emotion regulation and functioning.

**Methods/design:**

We present a double blind randomized controlled design. Remitted depressed adults will complete 10 online sessions of a cognitive control training targeting working memory functioning or a low cognitive load training (active control condition) over a period of 14 days. Effects of training on primary outcome measures of rumination and depressive symptomatology will be assessed pre-post training and at three months follow-up, along with secondary outcome measure adaptive emotion regulation. Long-term effects of cognitive control training on broader indicators of functioning will be assessed at three months follow-up (secondary outcome measures).

**Discussion:**

This study will provide information about the effectiveness of cognitive control training for remitted depressed adults in reducing vulnerability for depression. Furthermore, this study will address key questions concerning the mechanisms underlying the effects of cognitive control training, will take into account the subjective experience of the patients (including a self-report measure for cognitive functioning), and explore whether these effects extend to broad measures of functioning such as Quality of Life and disability.

**Trial registration:**

This study is registered with ClinicalTrials.Gov, number NCT02407652.

## Background

Improving the effectiveness of psychotherapeutic interventions for depression forms an important challenge for depression research. That is, patients who initially respond successful to therapy, often show residual symptoms which increases the chance of recurrence of depressive episodes. Moreover, existing treatments are less effective for chronic depression [1] and not all depressive symptoms show an equal response to treatment [2]. For instance, cognitive symptoms such as impaired executive- and working memory functioning and their biological substrates often remain present although the patient is considered to be in remission (e.g., [3, 4]). Importantly, it has been suggested that reduced cognitive functioning — i.e., impaired regulation of working memory, or ‘cognitive control’ — is not merely a byproduct of depression, but places remitted depressed (RMD) patients in a distinct vulnerable position for recurrence of depression [5, 6].

Indeed, the number of previous depressive episodes shows a negative correlation with behavioral indices of cognitive control [7]. Furthermore, prospective studies suggest that self-reported cognitive control impairments [8] and their behavioral indices [9] predict the development of future depressive symptomatology. Interestingly, impaired cognitive control has typically been linked to maladaptive emotion regulation strategies such as rumination [9–11], an important cognitive vulnerability factor for depression [12]. Especially brooding — a subtype of rumination that is characterized by a passive style of moody pondering — has shown to predict the occurrence of future depressive symptomatology [13]. Importantly, prospective studies indicate that the use of maladaptive emotion regulation strategies link impaired cognitive control to the development of future depressive symptomatology in RMD [14]. Thus, via maladaptive emotion regulation cognitive control impairments convey an important risk for recurrent depression (but see [15]). Moreover, this mechanism is believed to sustain and increase biological and cognitive vulnerability for recurrent depression (for a review, see [6]).

In accordance with studies indicating plasticity of executive and working memory functioning [16], these findings have led researchers to try to remediate cognitive control impairments in depression using cognitive training tasks. In a pilot study, Siegle et al. [17] demonstrated that combining treatment as usual (TAU) with a cognitive control training (CCT) shows potential in reducing rumination as well as depressive symptomatology in a limited MDD sample. The CCT existed of the adaptive Paced Auditory Serial Addition Task (PASAT; [18]) and Well’s Attention training [19]. Furthermore, Siegle et al. [20] have extended these findings, showing long term beneficial effects of CCT by demonstrating a reduced need for outpatient services at one year follow-up. Interestingly, whereas previous studies have demonstrated the potential of a combined CCT approach [17, 20–22], other authors have shown that the training component targeting working memory functioning (the adaptive PASAT) might suffice to reduce brooding [23] and depressive symptomatology [24] in MDD patients.

These first experimental findings are in line with existing conceptual frameworks concerning the role of cognitive control and rumination in recurrent depression [6, 25], suggesting that by remediating cognitive control impairments, one might decrease cognitive vulnerability for future depression. Accordingly, Siegle et al. [20] have suggested that effects of CCT on depressive symptomatology are preceded by changes in rumination. However, to date no experimental study has directly tested this mediation effect. Furthermore, previous studies have typically explored curative effects of CCT in MDD patients whereas only more recently the preventive potential of CCT has been explored in student populations. For instance, in a single session cognitive control manipulation, Cohen et al. [26] have demonstrated that inducing cognitive control while processing negative information buffers against negative effects of a subsequent rumination induction procedure (i.e., state rumination, rumination-related sad mood). Moreover, training inhibition of emotional information has shown to reduce rumination in at-risk students [27]. Interestingly, researchers have found that the adaptive PASAT shows promise in reducing stress reactivity and rumination in response to a lab stressor directly following training and a naturalistic stressor at one month follow-up in an at-risk student sample [28]. Furthermore, decreased stress reactivity in confrontation with a lab stressor predicted lower brooding levels following confrontation with naturalistic stress (i.e., examination period). These findings suggest that CCT targeting working memory functioning shows potential as a preventive intervention for depression.

### Rational for the proposed study

Previous studies indicate that the effects of CCT are not limited to the mere reduction of current depressive symptomatology in MDD patients, but might also extend to increasing resilience in at-risk populations. However, several theoretical gaps remain to be addressed.

First, in order to fully explore the potential of CCT targeting working memory functioning in reducing (cognitive) vulnerability for depression, a test of training effects in a RMD sample would be desirable. That is, RMD patients form a high-risk group for developing future depressive episodes [29] and prospective studies indicate that impaired cognitive control forms an important vulnerability factor in RMD [14]. Second, from a theoretical stance it would be interesting to explore the proposed mediational pathway from effects of CCT on rumination to reduced future depressive symptomatology. Third, with the exception of Siegle et al. [20] who explored effects of CCT on outpatient service use, previous studies have limited their scope to exploring effects of CCT on rumination and depressive symptomatology. We aim at extending previous findings by also exploring effects of CCT on adaptive emotion regulation as well as broader indicators of (dis-)functioning such as experienced disability, experienced remission from depression, and Quality of Life. Furthermore, we are not only interested in change in behavior indices of cognitive control, but also in the clinical experience of RMD patients concerning these cognitive factors (e.g., self-report measures of executive- and working memory functioning). Finally, in order to reduce sources of bias in exploring the potential of CCT as a preventive intervention, a rigid methodological approach — i.e., a double-blind randomized controlled trial (RCT) — is required.

## Method

### Design

We present a 2 (Condition) x 3 (Time) double blind, randomized controlled design. Adult RMD participants will be randomly allocated to either an online CCT intervention targeting working memory functioning or a low cognitive load training (active control condition). Both groups will perform 10 online training sessions over a period of 14 days, flanked by pre- and post-training lab assessments. Participants will return to the lab for a final assessment at three months follow-up (see Fig. 1 for an overview of the design). This study has been approved by the local ethical committee of the Faculty of Psychology and Educational Sciences of Ghent University and was registered with ClinicalTrials.gov, number NCT02407652.

**Fig. 1 Fig1:**
[figure not shown]
Study flowchart

### Participants

#### Inclusion and exclusion criteria

To be eligible for participation to this study, participants aged between 23 and 65 should report a history of depression (at least one prior depressive episode) and report stable (partial) remission (≥6 months). Consequently, participants should not meet criteria for a current depressive episode before starting training as assessed by the Mini-International Neuropsychiatric Interview (MINI; [30]). However, they should meet the criteria for a previous episode. The depressive episode should not have occurred in the context of a bipolar disorder. Neither should the participant report a history of psychosis, excessive substance abuse, or report experiencing cognitive impairments due to brain injury. A history of other comorbid disorders is allowed — yet these should not lead to current impairments — in order to increase the clinical relevance and validity of our study. Therapeutic maintenance contact (with a frequency less than once per three weeks) and use of antidepressant medication is allowed and will be registered. Importantly, antidepressant medication should be kept at a constant level throughout the course of the study.

#### Recruitment

RMD participants will be recruited using advertisements in popular (online) magazines and newspapers as well as flyers that were placed in 106 local drugstores (Ghent area). Furthermore, drawing on an existing database, 23 potentially interested participants will be contacted based on their interest in a prior prospective study of our lab (at that point, all of these participants had given their permission to be re-contacted in case a related study was planned). After having expressed interest in this study (i.e., by phone or e-mail), participants will be contacted by phone to provide further information and to screen eligibility based on a selection of relevant questions of the MINI screening version. To screen whether participants show a history of depression, we will ask questions concerning current and previous depressive symptoms, and collect information concerning the amount of episodes and past as well as current treatment. Furthermore, we will check whether (professional or similar) activities were resumed following the last depressive episode. If the participant seems eligible and is interested in participating in the study, he or she will be invited to the lab for a structured clinical interview (MINI). In the lab, the MINI screening version will be used to check for indicators of currently present comorbid disorders and — if this proves to be necessary — will be followed by the corresponding parts of the MINI interview to allow to control for presence of comorbid disorders. The parts related to MDD will be fully assessed to assure that participants do not meet the criteria for MDD before entering the study. Meeting eligibility criteria will allow the participant to enroll in the study, starting immediately with randomization over one of both conditions and the baseline assessment.

### Measures

#### Primary outcome measures

Rumination and depressive symptomatology form our primary outcome measures. *Rumination* will be assessed using the Ruminative Response Scale (RRS; [13, 31]). This 22-item questionnaire provides a total rumination score (range: 22 – 88), as well as Brooding and Reflection subscale scores (range: 5 – 20). Brooding is characterized by a passive style of moody pondering and is the most maladaptive form of depressive rumination [13, 32]. *Depressive symptomatology* will be assessed using the 21-item (range: 0 – 63) Beck Depression Inventory (BDI-II; [33, 34]). Both primary outcome measures exhibit adequate psychometric properties [13, 33, 34].

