### Sample size

We are the first to explore effects of CCT targeting working memory functioning in a RMD sample which makes it impossible to provide an exact estimate of effect size for the main outcome measure in this sample. However, previous work on MDD patients has yielded an effect size of *ɳ*^*2*^ = .19 for brooding [20], whereas work with at-risk undergraduate students revealed an effect size of *ɳ*^*2*^ = .11 in confrontation with naturalistic stress [28]. Given that this study will use an at-risk sample (RMD), we will base estimations of sample size on the latter effect size. In order to be able to detect a similar effect over two time points with *α* = .05 and 1-β = .80, the total sample size should at least be 68 (*n* CCT = 34, *n* active control = 34). We will stop recruiting once 68 participants have entered the training phase.

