### Analysis

In line with Consolidated Standards of Reporting Trials (CONSORT; [47]), we will use intention-to-treat (ITT) analysis to test effects of CCT on primary and secondary measures post-training and at follow-up. Missing data will be handled using the Last-Observation-Carried-Forward (LOCF) method. Effects of CCT will be tested using Repeated Measures, analysis of variance (ANOVA), or covariance (ANCOVA) with follow-up *t*-tests. Exploratory analysis will take into account potential moderators of training effects such as variability in baseline depressive symptomatology and cognitive control. ITT might not necessarily apply to the exploratory analyses such as analysis of process measures of training. As secondary analysis, we will also perform completers-only analyses. Explorative within-group mediation analysis will be performed using a stepwise regression approach [48] and the Preacher and Hayes [49] bootstrapping method.

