## Discussion

Prevention of recurrent depression is an important target for interventions. Previous findings indicate that CCT shows potential in reducing depressive symptomatology and rumination in MDD as well as cognitive vulnerability in at-risk undergraduate students. To test the potential of CCT as a preventive intervention for depression, the present study aims to test the effectiveness of CCT in a RMD sample. We will test whether CCT targeting working memory functioning — as compared to a low cognitive load training — can be used to reduce vulnerability for depression over a 3.5 months period. We hypothesize that CCT will have beneficial effects on primary outcome measures depressive rumination (i.e., brooding) and depressive symptomatology and hope to see these findings extend to adaptive emotion regulation and long-term functioning (secondary outcome measures).

This double blind RCT study forms a first test of the potential of CCT as a preventive intervention for depression in RMD. Furthermore, these findings will be informative to the literature as several exploratory questions will be addressed in order to further elucidate the role of cognitive control in vulnerability for depression. First, we will explore whether effects of CCT on depressive symptomatology are mediated by rumination. Second, we will explore whether effects of CCT extend to measures of adaptive emotion regulation and indices of functioning such as quality of life and disability. Third, in order to further elucidate the mechanisms involved during CCT, we could explore how process measures of CCT relate to effects of training.

Overall, this study will further enhance the knowledge on the role of cognitive control in emotion regulation and vulnerability for depression. This study forms a first step in testing the effectiveness of CCT targeting working memory functioning as a preventive intervention for (recurrent) depression. If these first results show to be promising, future work should focus on replicating the effects of CCT and exploring how this preventive intervention could best be implemented.

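### Two unranked primary outcomes, an unnamed primary RRS score and one unsplit .05: a claim resting on either outcome carries about 8-10% false positive risk, or 14-19% if each visit is tested separately

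*Protocol article*

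**What the plan says.** - **Outcomes.** Under Primary outcome measures: "Rumination and depressive symptomatology form our primary outcome measures". Neither is placed first. Depressive symptomatology is the BDI-II. Rumination is the RRS, which gives a total score "as well as Brooding and Reflection subscale scores". The section calls brooding the most maladaptive form but does not designate a primary score.
- **Hypothesis.** The Discussion expects "beneficial effects on primary outcome measures depressive rumination (i.e., brooding) and depressive symptomatology", so rumination is narrowed to brooding there.
- **Tests.** The Analysis section uses intention-to-treat analysis "to test effects of CCT on primary and secondary measures post-training and at follow-up". The methods are given as: "Effects of CCT will be tested using Repeated Measures, analysis of variance (ANOVA), or covariance (ANCOVA) with follow-up *t*-tests". The Design section describes 2 conditions by 3 times.
- **Alpha.** The only level in the article is in the Sample size section: "In order to be able to detect a similar effect over two time points with *α* = .05 and 1-β = .80", leading to 68 participants, 34 per arm, for an eta squared of .11.

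The article does not say whether one significant primary outcome is enough, whether both are needed, or in what order they are tested.

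**The concern.** With two primary outcomes and no stated rule, a reader may take a significant result on either one as support for the preventive effect of cognitive control training. Each test at .05 then adds its own chance of a false positive, and the error of the overall claim exceeds .05. Leaving the RRS score open in the section that defines the endpoints adds a further choice that could be made after the data are seen.

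This is more than a detail left to an analysis plan. Which score is primary and how the two primaries relate are endpoint definitions, and the sample size has already spent the whole .05 on one effect. A later correction that splits alpha would leave the trial below its stated power.

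**Working it through.** **1. Reproducing the sample size.** Inputs from the Sample size section: eta squared .11, alpha .05, power .80, two time points, two arms.

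- f² = .11 / (1 − .11) = .1236, so f = .352.
- Condition x Time with two time points is an F test with 1 and N − 2 degrees of freedom.
- With noncentrality λ = f²(N − 2), N = 68 gives λ = .1236 × 66 = 8.157 and power .804. At N = 66 the power is .791, so 68 is the smallest even total.
- With the other common convention, λ = f²N, the smallest even total is 66 (power .803).

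The plan's 68 is therefore reproduced with the full, undivided .05.

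**2. What a split of alpha would do at N = 68.** With λ = 8.157 and alpha = .025, power is .712 (.727 with λ = f²N). Restoring .80 at .025 needs N = 82. The sample size thus holds no reserve for a second primary outcome.

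**3. One Condition x Time test per outcome (two tests).** All effects null, each test at two-sided .05.

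- Independent: 1 − .95² = .0975.
- Correlated, by simulating bivariate normal test statistics with |z| > 1.96:

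| Assumed correlation between outcomes | Chance of at least one false positive |
|---|---|
| 0 | 9.8% |
| 0.5 | 9.1% |
| 0.7 | 8.3% |

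Simulating the 2 x 3 interaction F test itself, with 34 per arm and an assumed between-time correlation of 0.6, also gives about 8-10%.

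**4. Each visit tested separately (two outcomes x two visits, four tests).**

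- Independent: 1 − .95⁴ = .185.
- Between-outcome correlation 0.6 and between-visit 0.7, with cross-correlations as their product: 14.3%.
- Both correlations 0.7, same structure: 13.7%.
- All six pairwise correlations set to 0.7, a slightly stricter assumption: 13.1%.

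The range is about 14-19%, with 13% as the lowest value under the last assumption.

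**5. Which rumination score.** The Background singles out brooding as a predictor of later symptoms. Primary outcome measures calls it the most maladaptive form. The Sample size section cites a brooding effect from depressed patients, although it then sizes on a student effect without naming the score there. The Discussion states the hypothesis as brooding. None of these sections hypothesises an effect on Reflection. The intended score can be inferred, but the endpoint definition does not state it.

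**The case against.** **No section says that the tests are unadjusted.** That is an inference from silence. The document is a condensed article, and a correction could stand in an analysis plan that is not shown. This is right as far as it goes, so the point should not be read as proof that no adjustment exists. What stands is what the article itself fixes: two unranked primaries, no named RRS score in the endpoint section, and a sample size that works only with the undivided .05.

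**The number of tests may be only two.** A natural reading of the Design and Analysis sections is one Condition x Time test per outcome, with t-tests following it. That reading is fair and gives the lower range. The Analysis section does not say that the t-tests depend on a significant interaction, and it allows ANCOVA, which could be run per visit, so the four-test reading stays open.

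**A reader might infer a much larger error, up to about 25%.** That figure needs RRS total, Brooding, Reflection and BDI-II all to be tested as primaries at both visits (eight tests, assumed correlation 0.5). The article does not support this. It says that the questionnaire yields these scores, not that each is a primary endpoint, and its rationale and hypothesis point to brooding. Nor is the error several times .05 on the narrow reading: 9.8% is less than twice .05.

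**The hypothesis joins the two outcomes with *and*, and the article calls the study a first test.** If both had to be significant, the error would not be inflated. But a hypothesis of benefit on both is not a decision rule, and no rule is stated.

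**Conclusion.** The point holds at moderate size. The endpoint section leaves two primaries unranked and the RRS score unnamed, and the sample size assigns the whole .05 to one effect. If either outcome can carry the primary claim, the chance of a false positive is about 8-10% with one interaction test per outcome, and about 14-19% with separate tests at each visit.

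These figures rest on three assumptions: no true effect on either outcome, success on any one test being sufficient, and correlations from 0 to 0.7, which the article does not give. The direction does not depend on the exact correlation within that range, since every either-outcome reading there exceeds 5%.

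**What to change.** In Primary outcome measures, name RRS Brooding as the primary rumination score and list RRS total and Reflection as secondary.

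In Analysis, state that each primary outcome has one Condition x Time test; that Brooding is tested first at two-sided .05, and BDI-II at two-sided .05 only if Brooding is significant; and that per-visit t-tests are interpreted only after a significant interaction for that outcome. Both visits keep their present standing, so neither has to be demoted.

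**Cost.** BDI-II cannot be claimed as a primary result when Brooding is not significant. The first test keeps the stated .05 and .80 power, to the extent that the plan's two-time-point calculation describes that test. The change needs no additional participants.

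**Alternative.** Holm's procedure lets either outcome succeed alone, but its first step is at .025. If it is chosen, the Sample size section should restate the power for a single outcome at that step as about .71 at N = 68; N = 82 would be needed for .80. That choice is more than a change of wording.

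The article reports that recruitment is under way and that condition labels stay uninformative during the outcome analysis, so the rule can be fixed without knowledge of results by arm.
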